## Abstract

**Background:**

Impairments of the forearm, wrist, and hand affect a sizable proportion of individuals and impose a significant economic burden on health care systems. FEPSim is a medical device for hand and wrist rehabilitation. The FEPSim device could be part of the standard of care for upper extremity rehabilitation during therapeutic activities to increase range of motion, dexterity, and strength. FEPSim has not yet been tested in a health care setting; therefore, a trial of the effectiveness of FEPSim in upper extremity rehabilitation is warranted.

**Objective:**

This study aims to assess the feasibility of conducting a definitive trial in terms of recruitment, eligibility criteria, the type and number of diagnoses included, the length and dosage of the intervention, and data collection methods. This study also aims to gather clinical and statistical information as well as information related to the cost and usability, which allows for an economic evaluation of the device.

**Methods:**

The trial will use a randomized controlled design comprising 47 intervention participants and 47 control group participants. Participants will be adults (age≥18 years) attending outpatient rehabilitation with limitations in their forearm, wrist, or hand function due to distal radial or ulnar fractures, stroke, or osteoarthritis. This study’s primary outcome variables are related to patients’ range of motion and strength, specifically active and passive wrist flexion and extension range of motion; active and passive forearm pronation and supination range of motion; grip strength; and pinch strength. The secondary outcome variables are related to patients’ perceived wrist pain and disability in activities of daily living. The patients’ perceived wrist pain and disability in activities of daily living will be measured using the patient-rated wrist evaluation questionnaire. The control group will receive the standard of care at each of the 2 hospital facilities (Glenrose Rehabilitation and Royal Alexandra Hospitals). The intervention group will receive the same standard of care as the control group at each facility and will use the FEPSim device for therapeutic activities to increase strength, range of motion, resistance, and dexterity. All the participants will be assessed at baseline (week 0); weeks 2, 4, and 8; and postintervention (week 10).

**Results:**

The FEPSim study was launched in April 2020. This study is currently on hold because of the global COVID-19 pandemic. The recruitment process is expected to resume by September 2020, and the primary impact analysis is expected to be conducted by December 2020.

**Conclusions:**

This study will provide valuable information on the measurement of comparative intervention effects, technology acceptance by hand therapists, and how associated treatment and product costs will contribute to the evidence planning process, which will be crucial for the future adoption of FEPSim.

**Trial Registration:**

International Standard Randomized Controlled Trial Number Registry ISRCTN13656014; https://www.isrctn.com/ISRCTN13656014

**International Registered Report Identifier (IRRID):**

PRR1-10.2196/22145

## Introduction

### Background and Rationale

People affected by musculoskeletal disorders (MSDs) of the forearm and wrist, such as fractures (including those exacerbated by osteoporosis) and osteoarthritis, as well as people who have had a stroke will experience impairments of the upper limbs [1]. Impairments of the upper limbs affect functioning in everyday life and are correlated with a low quality of life [2]. Impairments of the forearm, wrist, and hand represent a health-related problem that affects a sizable proportion of individuals and impose a significant economic burden for health care systems. For example, in Alberta, Canada, by 2017, forearm fractures accounted for 17,031 cases with an incidence rate of 441 (new cases), the prevalence of osteoporosis accounted for 174,481 cases with an incidence rate of 18,603 (new cases); 21.00% (36,641/174,481) of people who have osteoporosis will have a fracture (eg, wrist fractures) [3]; the prevalence of different types of strokes accounted for 5277 cases with an incidence rate of 115 (new cases); 49.54% (2614/5277) of people who had a stroke also experienced an upper limb impairment; and the prevalence of osteoarthritis accounted for 449,561 cases with an incidence rate of 34,479 (new cases). The economic burden on Alberta’s health system as a result of caring for impairments of the forearm, wrist, and hand is significant and is expected to increase along with the projected increase in the age and size of the population. By 2017, the average cost of hospital inpatient care in Alberta totaled CAD $18,642,407 (US $15,287,926.24), an increase of 7.7% compared with the average cost in 2016 [4].

FEPSim, developed by Karma Machining & Manufacturing Ltd, is a medical device for hand and wrist rehabilitation. The FEPSim device could be part of the standard of care for upper extremity rehabilitation during therapeutic activities designed to increase range of motion, dexterity, and strength. These activities include controlled movements, strengthening, and exercises for retraining different grasp patterns that are used for activities of daily living and work tasks. Grading these activities is important to achieve therapeutic objectives and measure improvement. However, the equipment that is usually available in clinical settings does not allow therapists to ascertain their patients’ range of motion or the strength of their arms and hands (eg, wrist pronation or supination and flexion or extension) during functional hand movements and grasp patterns. FEPSim is a medical device that was developed for upper extremity rehabilitation and is used to strengthen the hand and wrist with movements such as wrist flexion and extension; hand and forearm pronation and supination; and different grasp patterns such as power grasp, spherical grasp, lateral grip, and disk grasp. FEPSim can be adjusted according to the patient’s capabilities during the rehabilitation process, thus allowing the therapist to grade the activities in terms of resistance and repetitions of any given exercise. FEPSim also allows the therapist to ascertain the patient’s strength and the degrees of range of motion that are achieved during active movements of the hand or forearm.

The FEPSim device appears to have potential advantages over current technologies. Hand therapy devices fall into 1 of the following 2 categories:

Low-cost and portable devices (average price: CAD $127.07 [US $104.16]) designed to offer specific hand therapies (eg, pronation or supination), such as *Rolyan Pronation/Supination* (CAD $188.57 [US $154.58]), or strengthen the forearm, such as *The Pronator* (CAD $108.64 [US $ 89.05]; a price list is available at Performance Health Trademarks [5]). The main disadvantage of these devices is that important measurements during hand therapy activities cannot be taken directly from them, and they are not adjustable.High-cost (portable and nonportable devices) commercial electromechanical devices designed to simulate the basic motions are required by the upper extremities in most occupations and to conduct hand therapy. This is the case for the Baltimore Therapeutic Equipment (BTE) work simulator and SaeboReJoyce [6]. For example, the estimated price of the BTE is between CAD $60,012.80 (US $49,193.99) and CAD $113,357.52 (US $92,921.99; email communication with the BTE Senior National Sales Representative) [7], whereas the SaeboReJoyce costs CAD $17,350.68 (US $14,222.79) [8]. The high cost of the BTE and SaeboReJoyce means that these devices are simply not affordable in many health care settings; thus, the FEPSim device could be a more affordable alternative for hand therapy purposes. The current prototype selling price of an FEPSim device is approximately CAD $6000 (US $4920; unit cost; eg, cost of goods sold). After evaluation and market analysis, to determine the scale of production, the FEPSim device should retail for less than CAD $1300 (US $ 1065.64) if the company adopts injection molding and brings in more purchased parts, with future models bringing costs down further. In addition, FEPSim has other potential advantages, such as compactness, portability, and ease of use.

Robots could be an alternative to assist in the rehabilitation process of the hand. However, these robotic systems are not yet available in hand therapy settings. A recent survey that aimed to examine patents and developments for hand rehabilitation robots found 28 systems, among which only 1, the Hand Exoskeleton Rehabilitation Robot, was designed to provide continuous passive motion (ie, the robot executes the motion of the patient’s upper limbs) as well as active independent movements (ie, the patient performs a motion according to his or her own ability) to the fingers and the thumb [9]. In another review, only 2 robotic devices were found for active independent movement of the hand [10]. All these robotic devices for hand rehabilitation were still in the prototype design phase, which corresponds to a technology readiness scale lower than 5 [11]; therefore, they have not yet been tested in real rehabilitation contexts.

### Hand Therapy: Existing Knowledge

The standard of care for rehabilitation for impairments of the forearm, wrist, and hand includes a combination of modalities and techniques such as immobilization, management of scar tissue, sensory modification, edema management, and therapeutic activities to increase the range of motion; dexterity and strength; and, ultimately, hand function [2]. The current evidence for the therapeutic standard of care activities depends on the medical condition and the strategies or modalities used to achieve therapeutic outcomes. In general, Roll and Hardison [2] found that for all MSDs, the strongest evidence for occupational therapy interventions supports postsurgical early active motion protocols and splinting for various conditions. However, few studies have shown significant differences in long-term outcomes among the compared interventions. For osteoarthritis, in particular, there is limited evidence that education and exercise can help patients regain function and reduce pain, whereas the evidence for the use of splinting for the same purposes is mixed. A systematic literature review summarized the outcomes of 26 studies for rehabilitation after distal radial fractures, finding that all the studies had low-quality designs and no clinically essential outcome differences among the modalities implemented in the interventions. The outcomes were categorized as functional (eg, range of motion, pain, grip strength, and activities of daily living), clinical (eg, residual soft tissue swelling), and resources (eg, number of outpatient attendances). The authors also found that, despite a lack of evidence for greater effects regarding long-term (3 months) goals, early occupational therapy led to more short-term improvements in gripping, pinching, and range of motion [12].

Strokes also affect hand function. The interventions that have been effective in managing spasticity are constraint-induced movement therapy, mirror therapy, and functional skill retraining. Furthermore, the recommended activities are passive range of motion (PROM) and active range of motion (AROM) activities, along with movements and functional activities with high levels of repetition [13]. Another review stated that a patient with a neurological condition that affects his or her hand movement (eg, stroke) needs to repeat a motion 300 to 400 times to learn a movement, but in current therapy sessions, the standard is closer to 30 repetitions. In a clinical setting, the recommended dosage would be a 60-minute session, 3 times a week for 6 weeks, where the use of technology can help achieve more repetitions in a shorter period of time [14]. Burns may also affect hand function. In general, the standard of care includes edema management, splinting, patient caregiver education, range of motion and strengthening, scar management, and retraining in activities of daily living [15]. We did not find any research that examined the evidence for these modalities. Finally, a literature review about the cost-effectiveness of physiotherapy interventions found only 2 studies about hand rehabilitation in neurological conditions. None of these studies reported any significant cost-effectiveness between the interventions under study. However, one study in which a high-tech device (ie, a robotic system) was used to support hand therapy showed that a group that used robot intervention used less health care, which reduced the overall cost [16].

### Evaluation Objectives and Research Questions

FEPSim has not yet been tested in a health care setting; therefore, a trial of the effectiveness of FEPSim in upper extremity rehabilitation is warranted. The primary objective of this study is to assess the feasibility of conducting a definitive trial in terms of recruitment, eligibility criteria, the type and number of diagnoses included, the length and dosage of the intervention, and the data collection methods. This study also aims to gather clinical and statistical information as well as information related to the costs and usability (adoption) of the new technology used in this study. Thus, this study has 6 secondary objectives:

To explore the clinical effectiveness of adding the FEPSim device to the standard of care for patients with injuries and clinical conditions of the forearm, wrist, and hand.To assess the outcome measures for measuring changes in the dependent variables.To gather and synthesize the data, from which the sample size of a definitive randomized controlled trial (RCT) can be estimated.To measure the key outcome domains (for completion rates, missing data, estimates, variances, and 95% CI for the differences between the intervention and control groups) for patients with injuries and clinical conditions of the forearm, wrist, and hand.To examine the total and component costs associated with the FEPSim device and with standard of care interventions for patients with injuries and clinical conditions of the forearm, wrist, and hand from an institutional perspective (ie, hospitals).To investigate the usability of the FEPSim device by therapists.

## Methods

### Study Design

This study will use a multimethod research design. The *Methods* section will be presented with regard to the objectives of the study.

### Primary Objective and Secondary Objectives 1 to 4: Research Design

The feasibility parallel-group RCT will follow the CONSORT (Consolidated Standards of Reporting Trials) guidelines for randomized feasibility studies [17]. The experimental group will receive an intervention consisting of sessions with the FEPSim device plus the standard of care, whereas the control group will only receive the standard of care for hand therapy.

### Secondary Objective 5: Study Design

For the economic evaluation component of this study, we will follow the Consolidated Health Economic Evaluation Reporting Standards [18] and Guidelines for the Economic Evaluation of Health Technologies: Canada [19].

### Secondary Objective 6: Study Design

For the usability component of this study, we will follow a qualitative description design [20].

### Study Setting

The study will be conducted in 2 health care facilities: the Royal Alexandra Hospital Outpatient Clinic and the Glenrose Rehabilitation Hospital Specialized Rehabilitation Outpatient Program Hand Class. Both institutions are located in Edmonton, Alberta, Canada.

### Eligibility Criteria

#### Inclusion Criteria: Participants (Patients)

This study will include outpatient adults (≥18 years) with limitations in their forearm, wrist, or hand function due to distal radial or ulnar fractures, stroke, or osteoarthritis (eg, patients who have undergone a wrist salvage procedure).

#### Inclusion Criteria: Participants (Therapists)

This study will include hand therapists from hand therapy services who have used the FEPSim device.

#### Exclusion Criteria: Participants (Patients)

Outpatients will not be included in our study if they (1) have chronic regional pain syndrome as these participants’ baseline measurements would differ too much and they would experience abnormal pain responses; (2) report subjective or patient limitations that prevent them from participating (eg, excessive pain and edema); (3) are unable to participate in the program (outpatient hand clinic) twice a week (eg, transportation and limited buy-in); (4) have limitations in their reading and listening comprehension of the English language that prevent them from understanding the patient-rated wrist evaluation (PRWE) questionnaire; or (5) have limitations in following instructions due to a severe cognitive impairment.

### Interventions

The eligible participants will be randomly assigned in a 1:1 ratio to either the experimental group or the control group.

#### Control Group

This group will receive the standard of care at each hospital, which consists of immobilization for 7 to 8 weeks (for fractures) after the time of the injury or surgery, followed by hand therapy sessions for 10 weeks to manage scar tissue, sensory modifications, and edema as well as therapeutic activities to increase strength, range of motion, and dexterity. These therapeutic activities will be carried out using the equipment and materials available at each hospital, including weights and elastic or gripping equipment and materials. The sessions’ length and frequency will depend on the patients’ needs and diagnoses. The length of each session will be between 30 minutes and 45 minutes, and they will be carried out once or twice per week.

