#### Experimental (Intervention) Group

This group will receive the same standard of care as the control group at each hospital, which consists of immobilization for 7 to 8 weeks after the time of the injury or surgery, followed by hand therapy sessions for 10 weeks to manage scar tissue, sensory alterations, and edema. The experimental group will use the FEPSim device for therapeutic activities to increase strength, range of motion, and dexterity. For this group, the sessions’ length and frequency will depend on the patients’ needs and diagnoses. The length of each session will be between 30 minutes and 45 minutes, and they will be carried out once or twice per week.

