#### Primary Objective and Secondary Objectives 1 to 4: Confounding Variables

The confounding effects of the participants’ age, gender, and medical condition (distal radial or ulnar fractures, stroke, or osteoarthritis); whether the participants are taking any pain medication; what activities the participants perform at home or work; and the therapist providing the intervention will be determined.

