### Allocation: Sequence Generation

Probability sampling stratified by medical condition (wrist fractures, acquired brain injuries, burns, or osteoarthritis) will be used. Random sequence generation will be prepared in advance by a research team member ([name]) on an Excel file spreadsheet (RAND function) using permuted block randomization with a block size of 4 and a ratio of 1:1.

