#### Secondary Objective 5: Estimating the Costs and Resource Use

To estimate the resource use and costs, we will use a single study–based economic evaluation approach (patient-level data). The costs will include resources related to the following categories: (1) the time human resources spend on the sessions will be monitored during the study, whereas the information on the average salaries of the human resources will be taken from the records at each hospital; (2) the capital cost of the equipment used in each intervention and depreciation of the equipment will be calculated using the straight-line depreciation approach; (3) therapeutic supplies (eg, weights and elastic or squeezing supplies); (4) consumables (eg, bandages and sanitization wipes); (5) cost of sterilization, if needed; (6) allowance costs (if any); and (7) maintenance costs (eg, calibration, preventive, and corrective maintenance of equipment). The information on the costs will be taken from the financial records at each hospital. In addition, we will conduct face-to-face interviews with the financial departments at both hospitals to identify the cost components and costing method.

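### Hospital defines both the local care and the cost source but enters neither the allocation nor the between-arm comparisons; a hospital term would remove avoidable chance noise at almost no cost

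*Protocol article*

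**What the plan says.** All references are to the protocol article.

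- **Setting.** "The study will be conducted in 2 health care facilities" (Study Setting). One is a hospital outpatient clinic, the other a hand class in a specialised rehabilitation outpatient programme.
- **Care.** For the control arm: "These therapeutic activities will be carried out using the equipment and materials available at each hospital" (Control Group). For the experimental arm: "This group will receive the same standard of care as the control group at each hospital" (Experimental (Intervention) Group), with FEPSim used for the therapeutic activities.
- **Costs.** "the information on the average salaries of the human resources will be taken from the records at each hospital", and "The information on the costs will be taken from the financial records at each hospital" (Data Collection Methods, Secondary Objective 5).
- **Allocation.** "Probability sampling stratified by medical condition (wrist fractures, acquired brain injuries, burns, or osteoarthritis) will be used", "using permuted block randomization with a block size of 4 and a ratio of 1:1" (Allocation: Sequence Generation). Hospital is not a stratum.
- **Covariates.** The Confounding Variables section lists age, gender, medical condition, pain medication, home or work activities and, last, "the therapist providing the intervention will be determined". Hospital is not in that list or among the covariates of Table 1.
- **Analysis.** Clinical outcomes are compared between arms with a t test or Mann-Whitney test. Covariate effects are to be explored in general linear or multilevel models where appropriate (Data Analyses, Primary Objective and Secondary Objectives 1 to 4). Each cost category is compared with a t test or Mann-Whitney test and a mean difference with 95% CI, and no adjustment is mentioned (Data Analyses, Secondary Objective 5).

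**The concern.** Hospital is the one variable that the protocol itself uses to define the equipment of the comparator and the source of the unit costs. It is known for every patient before randomisation. If outcomes or unit costs differ between the two hospitals, an arm that happens to have more patients from one of them shows part of that difference in its mean. The unadjusted comparison cannot separate this from the effect of FEPSim.

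At stake are the mean differences and 95% CIs for the clinical outcomes, which are meant to inform the sample size of a definitive trial, and the cost differences, which the Discussion says will inform purchasing decisions. The primary feasibility measures, retention and compliance, are not at issue.

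**Working it through.** The protocol gives no figure on hospital balance, so there is none to reproduce.

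**Inputs from the document:** N = 94, 47 per arm, 30% dropout (Sample Size); blocks of 4 within medical condition, 1:1 (Allocation: Sequence Generation).

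**Assumptions, because the document is silent:** hospital split p of 50:50 (70:30 as a variant); three conditions at 50/25/25%; hospital effect h of 0.25, 0.5 or 0.8 SD.

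**1. Imbalance in hospital mix.** Let D be the arm difference in the share of patients from one hospital.

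- Formula: SD(D) = √(4p(1−p)/N). For p = 0.5 and N = 94: √(1/94) = 0.103.
- A simulation of the stated scheme (5,000 trials per setting) gives:

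| Setting | SD of D (points) | P(D at least 10 points) | P(D at least 20 points) |
|---|---|---|---|
| N = 94, split 50:50 | 10.2 | 35% | 4.7% |
| N = 94, split 70:30 | 9.7 | 30% | 4.1% |
| N = 94, hospital share 80/20/50% by condition | 8.9 | 28% | 2.3% |
| N = 66, split 50:50 | 12.4 | 39% | 11% |
| N = 94, split 50:50, hospital added as a stratum | 2.4 | 0% | 0% |

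D is taken in either direction. N = 66 is 94 × 0.7 = 65.8, simulated as 66 randomised patients rather than as dropout from 94. Stratifying by condition does little for hospital balance, even when conditions cluster by hospital.

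**2. Shift in one realised estimate.** Shift = D × h. At a typical imbalance of 0.10:

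- 0.10 × 0.25 = 0.025 SD
- 0.10 × 0.5 = 0.05 SD
- 0.10 × 0.8 = 0.08 SD

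The standard error of the standardised difference with 47 per arm is 2/√94 = 0.206. The middle case is therefore 0.05/0.206, about a quarter of a standard error.

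**3. Precision.** The unadjusted SE relative to the within-hospital SE is √(1 + h²p(1−p)), which at p = 0.5 is √(1 + h²/4):

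- h = 0.25: √1.0156 = 1.008, or 0.8% larger
- h = 0.5: √1.0625 = 1.031, or 3.1% larger
- h = 0.8: √1.16 = 1.077, or 7.7% larger

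Adjustment has its own small price. With balanced margins the correlation of hospital with arm equals D, so the variance rises on average by about 0.102² = 0.0104, roughly 0.5% in the SE. The net gain is then about 0.3% (0.8 − 0.5) at the low end and about 7% (7.7 − 0.5) at the high end.

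**4. Costs.** The same rule applies. A 10-point imbalance carries one tenth of any hospital difference in cost per patient into the arm difference. If that difference were 30% (assumed), the shift would be 0.10 × 30% = 3%.

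**The case against.** **No documented hospital difference.** The protocol describes one standard of care for both hospitals, with the same session length, frequency and duration, and it says where costs are looked up, not that they differ. A reader might infer that care and unit costs do differ. No section says so, and every hospital effect used here is an assumption. This stands.

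**Chance is not bias.** Under 1:1 randomisation the expected imbalance is zero, and the ordinary unadjusted CI already allows for it. A reader might infer that the arm comparison is biased. It is not. What remains is that the noise can be removed.

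**Size.** One could take a 20-point imbalance with a 0.5 SD hospital effect, obtain 0.20 × 0.5 = 0.10 SD, and call that 40% of the stated target d = 0.25. That needs an imbalance seen in about 5% of trials. The target is also a poor yardstick, since 47 per arm has only about 22% to 23% power for it.

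**Therapist is already a listed confounder.** If each therapist works at one hospital, which is not stated, a therapist term would absorb hospital, and as a random effect it costs one variance parameter. But it belongs to exploratory clinical models only and is not applied to costs.

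**Exact model terms often sit in an analysis plan that is not shown.** This is fair. However, the article does state its strata, its confounder list and its between-arm tests, and the point concerns what those say.

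**Conclusion.** The point holds as a modest, nearly free improvement, not as an error that invalidates the trial. Hospital is absent from the strata, from the covariates and from both between-arm comparisons, although care and costs are organised by hospital. At N = 94 and an assumed 50:50 split, the imbalance has an SD of about 10 points, a typical shift is 0.025 to 0.08 SD, and the SE is about 0.8% to 8% larger, for assumed hospital effects of 0.25 to 0.8 SD. If the true hospital effect is near the low end, little is gained. The case is clearest for costs, where no adjustment of any kind is stated.

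A reader might conclude that the allocation must be stratified by hospital. The document does not support that as a requirement. Blocks are fixed at 4, therapists are not blinded, and therapist researchers recruit. A list for each hospital would make the next allocation easier to predict.

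**What to change.** 1. Add hospital to the Confounding Variables list and to the covariates of Table 1.
2. Estimate the between-arm clinical and cost differences and their 95% CIs from a model with hospital as a fixed effect, alongside medical condition, which is already the stratum. The plain t tests can remain as a supporting analysis.
3. Report costs by hospital, so that a reader can see whether the two differ.

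The hospital term costs one degree of freedom, about 0.5% in the SE at N = 94, and needs no extra patients or data.

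Stratifying the list by hospital is optional. It would cut the SD of the imbalance from 10.2 to 2.4 points. Against that, it doubles the strata (the four conditions named for allocation become eight cells for 94 patients), leaves more incomplete blocks, and makes allocation more predictable with a fixed block of 4 in an open-label trial.
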